# Statistical Analysis

## Sample size calculation

## The sample size is determined by the number of patients eligible for inclusion in the study who are seen in each hospital during the inclusion period. Thirty patients will be included in each of the following groups: control group, conventional rehabilitation group and telerehabilitation group. For the calculation of the power of the study, a 12% possible loss to follow-up has been estimated. Thus, accepting an alpha risk of 0.05 in a bilateral test with 27 subjects in the control group and 27 patients in the intervention group, the power of the hypothesis test is 95% to detect as statistically significant the difference between the mean of 5000 in the first group and the mean of 4000 in the second group after rehabilitation. Based on the potential impact of the telerehabilitation intervention on compliance with the physical activity recommendation at 10 months follow-up, and considering METs-minutes/week as the unit of measurement, it has been estimated that patients in the intervention group will perform 5000 METs-minutes/week while in the conventional rehabilitation group they will perform 4000 METs-minutes/week. It is estimated that physical activity in the non-rehabilitation group will be significantly lower.

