## Methodology of statistical analysis

The characteristics of the patients in the two study groups will be described (applying the appropriate estimators according to the type of variables, such as means and confidence intervals, medians and interquartile ranges or proportions) and possible differences between the groups will be assessed using appropriate statistical tests of differences of means, distributions of ranks or proportions. The comparison of the primary variable and the secondary variables of the study in both groups at baseline, at four months and 10 months after the start of rehabilitation will be carried out using Pearson χ2 test for qualitative variables (Fisher exact test for dichotomous variable) or Student t-test for independent samples for quantitative variables (Mann-Whitney U test when parametric assumptions couldn’t be assumed). The treatment effects within groups (at four months or ten months) will be assessed using McNemar-Bowker test of symmetry for qualitative variables (McNemar test for dichotomous variable) or Student t-test for paired samples for quantitative variables (Wilcoxon signed-rank test when parametric assumptions couldn’t be assumed). The relationship between quantitative variables will be assessed by Pearson’s correlation coefficient (Spearman’s rank correlation coefficient when parametric assumptions couldn’t be assumed). Multiple linear regression models will be used to assess the significance and magnitude of the intervention effect controlling for possible differences in patient characteristics between groups. In general, backward-forward models will be used, initially constructing the complete models and excluding non-significant variables one at a time (p for variable removal: 0.10) but trying to include the previously removed variables after each exclusion (p for incorporation: 0.05. The analysis will be performed on an intention-to-treat basis. For the economic evaluation, the unit cost will be obtained by quantifying the consumption of resources and applying the official cost rates of the Valencian Health Agency or, if these are not available, they will be estimated by assessing the time and cost of the resources involved. Two-sided exact p-values will be calculated whenever possible and p-values ≤ 0.05 were considered statistically significant. Data will be analysed using IBM SPSS Statistics 22 and R 4.0.2 for Microsoft Windows.

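### The adjusted intervention effect is estimated after stepwise covariate selection in about 54 patients, so its standard error is too small and its p-value does not hold the 5% level

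*Protocol*

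**What the plan says.** The same text stands in the protocol summary (Data Analysis) and in Methodology of statistical analysis. It first plans an unadjusted comparison of the arms at each time point, by Student t-test or Mann-Whitney test for quantitative variables. It then adds a regression with an inferential purpose: "Multiple linear regression models will be used to assess the significance and magnitude of the intervention effect controlling for possible differences in patient characteristics" between the groups.

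The rule for building that regression is fixed: "In general, backward-forward models will be used, initially constructing the complete models and excluding non-significant variables one at a time". The thresholds are "p for variable removal: 0.10" and, for re-entry, "trying to include the previously removed variables after each exclusion (p for incorporation: 0.05". The significance rule is "Two-sided exact p-values will be calculated whenever possible and p-values ≤ 0.05 were considered statistically significant".

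The text does not name the candidate covariates, cap their number, state that the treatment term stays in the model, or correct for selection. It also does not rank the unadjusted and adjusted results.

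**The concern.** A p-value from linear regression is valid when the model was fixed before the outcome was seen. Here the outcome chooses the model. Covariates that fit by chance are kept, so the residual variance looks smaller than it is, and the final treatment test is read as though those covariates had been named in advance. The effect grows with the number of candidates relative to the number of patients, and this trial is small.

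At stake is the adjusted estimate of the primary comparison. With no stated ranking, a non-significant t-test and a significant stepwise regression could both be reported, and the one with the understated error could carry the conclusion.

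**Working it through.** **Inputs.** Sample size calculation: "accepting an alpha risk of 0.05 in a bilateral test with 27 subjects in the control group and 27 patients in the intervention group", so n = 54. Thresholds 0.10 and 0.05 and the two-sided 0.05 test come from Methodology of statistical analysis. The candidate count is not stated, so it is varied.

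**The plan's own figure.** The stated 95% power is for a difference between means of 5000 and 4000, with no SD given. Solving backwards with SD = 1000: 1000 / (1000 × √(2/27)) = 3.674, and Φ(3.674 − 1.960) = Φ(1.714) = 95.7% (noncentral t: 95.0%). The figure is reproduced with an assumed SD of about 1000. It describes a two-sample comparison of means, not the regression.

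**How many candidates?** Variables lists 19 clinical items, 1 baseline work item (active worker), 6 examination, 7 exercise-test, 1 pulse wave velocity and 8 laboratory items: 19 + 1 + 6 + 7 + 1 + 8 = 42. At least five could hardly serve as baseline covariates. ST decline and angor are ruled out by the entry exercise test. Stable angina is outside the enrolled population. Statins are planned for patients at discharge. One indicator of coronary syndrome type is redundant. That leaves 42 − 5 = 37 as a practical ceiling from that list.

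**Simulation.** 27 + 27 patients, no treatment effect, normal outcome, independent normal covariates unrelated to outcome. Start from the full model, remove the least significant covariate while p > 0.10, and retry removed ones at p < 0.05 after each exclusion. Treatment is kept in and tested at 0.05 in the final model. The main run used 2000 trials per row (Monte Carlo error about 0.5 to 1 point). Where a range is shown, separate runs of the same rule gave slightly different values; the 24% comes from a run of 500.

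| Candidates | False-positive rate | Reported SE ÷ true SD |
|---|---|---|
| 5 | 5.6–6.4% | 0.96 |
| 10 | 6.6–7.1% | 0.91–0.92 |
| 19–20 | 8.9–11.5% | 0.82–0.84 |
| 30 | 14.0% | 0.74 |
| 37 | about 19–24% | 0.62 |

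**Cross-check.** If the reported SE is a fraction r of the true SD, the test rejects at about 2.01 × r true SDs, so the error rate is roughly 2 × [1 − Φ(2.01 r)].
- r = 0.92: 2.01 × 0.92 = 1.85, giving 6.4%.
- r = 0.84: 1.69, giving 9.1%.
- r = 0.74: 1.49, giving 13.6%.
- r = 0.62: 1.25, giving 21.1%.

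These agree with the table, so the understated SE accounts for the inflation.

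**Controls.** Across the main-run scenarios the unadjusted t-test rejected in 4.1–5.8% and the full model without selection in 4.0–5.7%. The fault is the selection, not the adjustment. With 20 candidates, of which five are truly prognostic, the stepwise rate is 11.8% (SE ratio 0.80). With 20 noise candidates and treatment itself open to removal it is 9.6%.

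**The case against.** The strongest reply is that the size rests on a count the protocol never gives. It speaks only of patient characteristics, and a statistical analysis plan may name a short list. With five candidates the inflation is negligible. This stands as a limit on the size. It does not rescue the rule, because the protocol itself fixes the selection procedure and a plan that follows it inherits the fault.

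Three stronger readings are tempting, and the documents do not support them.

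- A reader might put all 42 listed items into the model and infer a false-positive rate near 30%. The list stands mostly under secondary variables and mixes patient characteristics with outcomes. Nothing says that all of it enters, and about five items would be constant or redundant at baseline.
- A reader might infer that a non-significant treatment term is deleted, so that no effect is reported. That is only a literal reading. The regression's stated purpose is to estimate the intervention effect, which suggests that selection applies to the controls, and the unadjusted comparison would be reported anyway. What remains is that no rule says treatment stays in.
- A reader might infer that the trial has no fixed analysis at all. The two-sample comparison, on which the power statement rests, involves no covariate selection.

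The baseline comparisons between arms ("possible differences between the groups will be assessed using appropriate statistical tests of differences of means") are uninformative after proper randomisation but do not cause the inflation. The protocol does not say that they choose the covariates.

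**Conclusion.** The point holds for the adjusted analysis only. The direction is firm: selection at 0.10 and 0.05 on the tested outcome, in about 54 patients and without correction, understates the standard error and raises the false-positive rate above 5%. The size is conditional on the number of candidates. It is slight at five, about 7% at 10, 9–12% with roughly the 19 clinical variables, and about 19% or more if nearly all listed variables enter. These figures assume independent normal noise covariates with treatment retained. Many real candidates are binary or overlapping, so they are a guide rather than a prediction. The unadjusted t-test or Mann-Whitney comparison is sound on this point, which makes this a correction the plan should have rather than a fatal fault. The missing ranking of the two results is what would let the distorted one matter.

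**What to change.** In both places (the summary's Data Analysis and Methodology of statistical analysis), delete the backward-forward procedure. Replace it with one pre-specified linear model for METs-minutes/week at 10 months in which treatment is always retained and a short covariate list is named in advance: baseline METs-minutes/week, with recruiting hospital as an option. State whether this model or the unadjusted comparison is primary. Report any other covariate set as a labelled sensitivity analysis, and state that covariates are not chosen from baseline significance tests.

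The cost is wording. The IPAQ is already completed at baseline, so no new data are needed. How well the baseline score predicts the 10-month score is unknown here, but a covariate fixed in advance keeps the test at its level even if it predicts poorly, as the unselected models above show. The downside is that a chance imbalance in an unlisted variable is addressed only in a sensitivity analysis.

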## Economic evaluation: cost-effectiveness analysis

The study includes a cost-effectiveness analysis to assess the costs and impact on health-related quality of life of the telerehabilitation intervention compared to in-hospital rehabilitation and the control group. The cost analysis will be carried out from the funder's perspective, including direct health care costs (pathology-related emergency visits, hospitalisations for the same cause, diagnostic and therapeutic tests such as revascularisations...) during follow-up. It will also include the costs derived from the intervention, which in the case of conventional rehabilitation, the programd schedule includes 16 rehabilitation visits, 8 rehabilitation sessions (with a physiotherapist, a nurse and a nursing assistant per session) and 8 educational talks. In the telerehabilitation group, the schedule includes 4 rehabilitation visits, 3 sessions (with a physiotherapist and a nurse) and 4 educational sessions. Unscheduled visits and sessions during the follow-up will also be included. The unit costs will be obtained from the Generalitat Valenciana catalogue.

Additionally, an analysis will be performed from a social perspective, including also indirect health care costs due to lost productivity of the patient (number of sick leaves and time to return to work after the event). Indirect costs will be reported by the patient in the follow-up data collection logbook. Effectiveness will be assessed by the physical activity performed by the patient, reported by the patient at the end of the follow-up, measured in METs-minutes/week.

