# Study Design

## Type of Study

Phase III clinical trial, feasibility, controlled and randomised, with two branches (intervention group by cardiac telerehabilitation and conventional rehabilitation control group in the hospital), developed in the cardiology service of the Hospital Arnau de Vilanova and Hospital Universitari i Politècnic La Fe.

The trial will be randomised, as the inclusion of each patient will be randomised by a unit external to the researchers, which will establish to which group the patient will be assigned. However, the characteristics of the interventions do not allow the study to be blinded either for the patient or for the professional. However, the analyses, stress tests and shuttle tests will be performed in a masked manner without the assigned group being identifiable by the investigators carrying out the examinations.

Sixty patients after acute coronary syndrome from two hospitals will be included.

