- Talk: Diet and nutrition: 30m

- Third exercise session: 60m

Ambulatory phase: from week 3 until the end of the trial at week 40, the patient should perform his physical exercise routines 4 times per week monitored by the ITS. These routines can be performed by walking outdoors. The patient's application on the mobile phone, allows the heart rate to be calculated for each exercise session. The system alerts about possible deviations from the programed training heart rate so that the patient can adjust their physical activity to achieve the recommended frequency. All this data is also transmitted to the platform for subsequent analysis by the professional. The application is not only a means of controlling and monitoring the quality of physical exercise, but also fundamentally a tool to assist in cardiovascular prevention in a comprehensive way. This means that the patient's cardiovascular risk factors will be recorded, in order to help the patient modify their lifestyle and correct or minimise the risk factors that contribute to disease progression. The support website includes personalised aids (information, education, motivational messages) so that the patient can self-manage their daily life and feel protected and in control.

The educational program will consist of 6 lectures on the following topics:

- Telerehabilitation program

- Information on coronary heart disease and cardiovascular risk factors.

- Anxiety and depression in the context of an acute coronary event.

- Sexuality and return to work after an acute coronary event

- Heart-healthy diet and the benefits of physical exercise.

- Smoking.

The technology available to patients in the telerehabilitation group includes the following:

A. Comprehensive telerehabilitation system

The Integral Telerehabilitation System (ITS) is a software and services platform created by Nabelia (http://nabelia.com/es/) to establish Cardiac Prevention and Rehabilitation Programs (CPRP) aimed at helping the management and personalised management of cardiovascular risk factors, with the highest quality but in a cost-effective manner for the healthcare centre and professionals. Its objective is to provide continuous, long-term care and support to patients with CVD during their recovery process.

The ITS to be configured for the study consists of the following elements:

1) Web-based application for the practitioner in the hospital, which allows to:

o Advise the patient on their personal care plan

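### The cost analysis in section 9.4 counts only pathology-related emergency visits and same-cause admissions, so it omits the acute-care cost of non-cardiac injuries caused by the exercise programmes

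*Protocol*

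**What the plan says.** Cost per patient per month is a named secondary objective (Protocol section 4.2). Section 9.4 sets out how cost is built up.

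- **Acute care, funder's perspective:** "direct health care costs (pathology-related emergency visits, hospitalisations for the same cause", then "diagnostic and therapeutic tests such as revascularisations...) during follow-up".
- **Delivery of the programmes:** the scheduled visits, sessions and talks in each arm. For telerehabilitation, "the schedule includes 4 rehabilitation visits, 3 sessions (with a physiotherapist and a nurse) and 4 educational sessions". The next sentence but one or so adds: "Unscheduled visits and sessions during the follow-up will also be included".
- **Social perspective, as an additional analysis:** lost productivity, namely "number of sick leaves and time to return to work after the event".
- **Effectiveness:** patient-reported physical activity at the end of follow-up, in METs-minutes/week.

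On harms, section 8.2 defines an adverse reaction as any undesirable event after the programme has started. The opening of section 8 asks the investigator to obtain enough information to judge causality. Section 9.4 does not refer to these records. The notebook in Annex 1 (month 4 and month 10 visits) records emergency consultation and hospitalisation as yes or no, without cause, number or length of stay.

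**The concern.** Both arms receive an exercise programme, and exercise can injure people in ways unrelated to their coronary disease. The qualifiers on emergency visits and admissions in section 9.4 refer to the pathology under study, not to the intervention under study. An injury sustained in a prescribed session is a consequence of the programme, yet its acute-care cost falls outside the rule.

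At stake is the balance of the cost-effectiveness comparison. Its effect measure is the amount of exercise itself, so a programme that produces more exercise gets full credit for it. If that exercise also produces non-cardiac injuries, their emergency and hospital costs do not enter the other side of the ratio.

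**Working it through.** The protocol states no figure that could be reproduced here: it gives no injury rate, no unit cost and no expected cost difference. The check is therefore mainly a reading of the text, with arithmetic showing what can and cannot be said about size.

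**1. Which events are costed under section 9.4, funder's perspective?**

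| Event during or caused by the programme | Costed? | Reason |
|---|---|---|
| Ischaemic event, cardiac readmission or revascularisation triggered by exercise | Yes | Related to the pathology |
| Emergency visit for a fall or muscle injury in an exercise session | No | Not related to the pathology |
| Admission for a fracture in an exercise session | No | Not for the same cause |
| Extra rehabilitation visit or session | Yes | Unscheduled visits and sessions |

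The gap is the emergency and hospital cost of non-cardiac injury.

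**2. Can the rule be applied from the event items?** Not from those items alone. They carry no cause, so a pathology-related visit cannot be told from any other. They carry no count or length of stay, so a cost cannot be built from them. The adverse reaction records or the medical history would have to supply this.

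**3. Direction.** Let k_T and k_C be the omitted cost per unit of activity in the telerehabilitation and conventional arms. Section 9.1 plans for 5000 and 4000 METs-minutes/week. The omitted difference in mean cost is

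D = 5000·k_T − 4000·k_C.

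- If k_T = k_C, the omitted cost in the telerehabilitation arm is 5000/4000 = 1.25 times that in the conventional arm, and the rule favours telerehabilitation.
- D is zero when k_T/k_C = 4000/5000 = 0.80 and negative below that.

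The protocol gives no information on k_T/k_C. The type of exercise differs: walking in one arm, a supervised circuit with step and knee-lift stations in the other. Equality cannot be taken for granted. The 5000 and 4000 are also planned values for total activity after rehabilitation, not for activity under the assigned programme, so this is an indication only.

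**4. Size.** Section 6.4 states that "from week 3 until the end of the trial at week 40, the patient should perform his physical exercise routines 4 times per week". Weeks 3 to 40 inclusive are 38 weeks, and 38 × 4 = 152 prescribed home sessions per patient (148 if 37 weeks are counted). For 30 patients with full attendance, 152 × 30 = 4,560 sessions. The injury rate must be assumed:

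- 0.1 per 1,000 sessions: 4,560 × 0.1/1,000 = 0.5 events
- 1 per 1,000 sessions: 4.6 events
- 2 per 1,000 sessions: 9.1 events

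The range runs from less than one event to nine in that arm. It says nothing about the conventional arm, and therefore nothing about the difference between arms.

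**The case against.** The case for leaving the text alone has four parts.

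*The list is open and other costs are included.* The direct-cost list ends in an ellipsis, intervention costs and unscheduled visits are added with no limit by cause, and sick leave is counted. It is therefore true that section 9.4 does not count cardiac care alone. But the ellipsis follows the tests and revascularisations and does not lift the qualifiers on visits and admissions. The intervention costs are spelled out as visits, sessions and talks, and the unscheduled contacts read naturally as more of the same. Sick leave enters only the social perspective and does not bring hospital costs back.

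*Harms are recorded anyway.* They are, with causality, and section 8.1 requires all adverse events to be tabulated in the reports. This stands, and it makes the remedy cheap. It does not put the cost into the cost analysis.

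*Disease-related costing limits noise with 30 patients per arm.* This is a fair reason to keep all-cause costs out of the main analysis. It is not a reason to exclude events that the intervention itself caused.

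*Attribution detail can be left to the analysis plan.* Detail can, but here the protocol itself fixes the restriction.

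Two stronger readings are tempting. A reader might set the 152 home sessions plus 3 hospital sessions against the 8 exercise sessions of the conventional arm and infer a large imbalance in exposure to injury. The protocol does not support that. It expects conventional patients to reach 4000 METs-minutes/week, so they are far from inactive outside those sessions. The home sessions, though without staff present, are remotely monitored: the system tracks heart rate, alerts the patient and sends the data to the professional. Patients with limiting musculoskeletal disorders are also excluded. A reader might also infer that unblinded staff decide what is pathology-related. Section 6.1 says the interventions "do not allow the study to be blinded either for the patient or for the professional", but no section says who classifies events for costing.

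**Conclusion.** The point holds in a limited form. Followed as written, section 9.4 leaves out of the funder-perspective analysis the emergency and hospital costs of non-cardiac injuries caused by the assigned exercise, while the effect measure credits the exercise in full. Exercise-triggered cardiac events are counted, so it would be wrong to say that the programme's harms as a whole are omitted.

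The omission may understate the cost of the more active arm. That telerehabilitation is favoured is not shown: it would follow if the omitted cost per unit of activity were the same in both arms, which is an assumption. The size cannot be given without an injury rate and unit costs, and the protocol has neither. The matter concerns a secondary objective and leaves the primary comparison untouched. It is worth correcting because the correction is easy and removes a one-sided rule.

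**What to change.** 1. In section 9.4, widen the costed events to emergency visits, admissions and tests that are related to the coronary disease *or attributed to the assigned exercise programme*. Take the attribution from the adverse reaction records and causality information in section 8, and state that attribution for costing is made without knowledge of the arm where feasible. Masking will sometimes fail, because the circumstances of an injury can reveal the programme.
2. In Annex 1, record cause, number and length of stay beside the emergency consultation and hospitalisation items at months 4 and 10.
3. Report all-cause emergency visits and admissions as a sensitivity analysis. This also guards against a weakness of attribution: a walk in month 6 is programme exercise in one arm, and may not be classed as such in the other, whose hospital programme ends after 8 weeks.

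The cost is one sentence in the protocol, a few more notebook fields and a sensitivity estimate that will be noisier than the main one with 30 patients per arm.

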## Methods

After explaining the fundamentals of the study to the patients and accepting their participation, they will sign the informed consent form. The first procedure will be to perform a symptom-limited treadmill exercise test with oxygen consumption, seven to ten days after hospital discharge, using the Bruce protocol. If the test results allow inclusion in the study, demographic data, clinical history, physical examination and analytical data will be completed in the data collection notebook. The baseline surveys will be completed, the procedures to be followed will be explained, as well as the schedule of the various activities included in each of the groups. Patients shall receive medication as deemed appropriate by the physician at the time of discharge from hospital, with the initial goal of achieving LDL of 70 mg/dl or less, blood pressure of 140/90 mmHg or less and, where appropriate, glycosylated haemoglobin of less than 7%.

The follow-up period will be 10 months in both groups. The differences in follow-up are detailed below.

At the end of the 10-month follow-up period, all subjects included in the study will undergo a stress test, final analysis and completion of the various outcome evaluation surveys.

Control Group A.

Patients in Control Group A will come to the hospital twice a week during the 8 weeks of the conventional rehabilitation program. Eight sessions will be devoted to physical exercise and another eight sessions to education in various aspects. At the end of the hospital phase, outpatient follow-up by primary and specialised care will be carried out. Subjects will visit the hospital a total of 16 times during 8 weeks to perform the exercises included in the hospital protocol, supervised by a physiotherapist and a nurse from the Cardiology Service.

The protocol includes:

Preparation to start the activity (Warm-up).

15 minutes of low impact cardiovascular exercise plus stretching and flexibility.

Stretching:

8-10 seconds interspersed with activities that maintain heart rate such as walking in place.

Musculature involved: triceps sural, hamstrings, quadriceps, deltoids, paravertebral and pectoralis.

The circuit:

The circuit is designed to cater for all patients with varying functional abilities. It provides the opportunity to increase cardiovascular work time. It is organised as explained in the following diagram:

| **LEVEL** | Group session content |
| --- | --- |
| 1 | 1 CV station followed by 1 min. Of AR |

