## Data collection

The following data shall be collected on all patients at baseline, at 4 months and at 10 months.

1. Demographic data: initials of name, age, sex, identification number).

2. Clinical data: STEMI, NSTEMI, unstable angina, stable angina, number of vessels, number of stents, complete revascularisation, active smoking, ex-smoker, hypertension, dyslipidaemia, diabetes mellitus, left ventricular ejection fraction, beta-blockers, ACEI/ARBs, statins, dual antiplatelet therapy.

3. Socio-occupational data: active worker, return to work after discharge.

1. Physical examination: systolic blood pressure, diastolic blood pressure, heart rate, body mass index (BMI), waist circumference, hip circumference.
2. Analytical data: glucose, creatinine, total cholesterol, LDL cholesterol, HDL cholesterol, triglycerides, CRPus, HbA1c.
3. Pulse wave velocity.
4. Surveys: EQ-5D, IPAQ, HAD, Adherence to Mediterranean diet, Fagerström test (if active smoking).
5. Clinical events: emergency department, readmission, revascularisation.

The following data will only be collected at baseline and at 10 months.

1. Exercise test: VO2max, exercise time, maximum heart rate, maximum blood pressure, recovery time, ST decline, angor.

The following data will only be collected from patients in the intervention group:

1. Every 15 days: weight, smoking, waist circumference, systolic pressure, diastolic pressure, heart rate, visual anxiety-depression thermometer, fruit consumption, vegetables, wine/beer consumption.

2. At 4 and 10 months: survey of satisfaction with the application.

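### The economic evaluation asks about quality of life but measures only self-reported activity; its cost list does not name the telerehabilitation system, and its control staffing disagrees with the programme description

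*Protocol*

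**What the plan says.** Protocol section 9.4 opens with its purpose: to "assess the costs and impact on health-related quality of life of the telerehabilitation intervention". Later in the section it fixes the outcome: "Effectiveness will be assessed by the physical activity performed by the patient, reported by the patient at the end of the follow-up", in METs-minutes/week. EQ-5D is not mentioned there, although section 6.5 collects it ("Surveys: EQ-5D, IPAQ, HAD, Adherence to Mediterranean diet") and Annex 1 has a field for it at the randomisation visit and at month 10.

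On costs, section 9.4 states in general terms that the costs of the intervention are included, and then describes each arm's schedule.

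- Telerehabilitation: "In the telerehabilitation group, the schedule includes 4 rehabilitation visits, 3 sessions (with a physiotherapist and a nurse) and 4 educational sessions".
- Control: 16 visits, made up of "8 rehabilitation sessions (with a physiotherapist, a nurse and a nursing assistant per session") and 8 talks.

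Section 6.4 describes the control sessions as "supervised by a physiotherapist and a nurse from the Cardiology Service". For telerehabilitation, section 6.4 describes a system-monitored phase from week 3 to week 40, with a phone application, a sensor garment and review of transmitted data: "All this data is also transmitted to the platform for subsequent analysis by the professional".

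Section 9.4 takes unit costs from the regional catalogue. Section 9.3 adds that resources without an official rate will be estimated from the time and cost involved.

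**The concern.** Three things in section 9.4 do not fit together or do not fit the rest of the protocol.

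- **Effect measure.** A ratio of cost to METs-minutes/week says nothing about health-related quality of life, which is the effect named at the start of the same section. If the section is followed as written, that question goes unanswered although the instrument for it is already in use.
- **Telerehabilitation costs.** The itemised contacts are those of the two hospital weeks. What distinguishes the arm is what follows, and the resources of that phase are not named. An analyst working from the list and the catalogue alone could leave them out. The secondary objective asks for the cost per patient and month of the extended programme, so this phase is central to it.
- **Control costs.** A costed input, staff per exercise session, differs between section 9.4 and the programme description.

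At stake is the credibility of one secondary objective. The primary comparison is unaffected.

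**Working it through.** No prices appear in the protocol, so only counts can be checked.

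**Contacts (sections 6.4 and 9.4)**
- Control: 8 exercise + 8 education = 16 visits. This reproduces the 16 in section 9.4.
- Telerehabilitation: section 6.4 gives 4 hospital attendances with 3 exercise and 4 education sessions. This agrees with section 9.4.

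The visit counts are therefore right. The question is what is attached to them.

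**Staffing of exercise sessions (staff-sessions = sessions × staff)**
- Control with section 9.4 staffing: 8 × 3 = 24.
- Control with section 6.4 staffing: 8 × 2 = 16. Difference: 24 − 16 = 8.
- Telerehabilitation with section 9.4 staffing: 3 × 2 = 6.

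The nursing assistant appears only in section 9.4. These are group sessions, so the counts are per group session and not per patient.

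**The system-monitored phase (section 6.4)**
- Duration: 40 − 3 + 1 = 38 weeks.
- Scheduled exercise sessions at 4 per week: 38 × 4 = 152.
- Share of all scheduled exercise sessions in the arm: 152 / (152 + 3) = 152 / 155 = 98%.

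The 3 hospital sessions are itemised. The resources behind the other 152 are not. The month-4 and month-10 forms in Annex 1 have no field for professional review time.

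**Where EQ-5D stands**
- Section 6.5 schedules the surveys at baseline, 4 months and 10 months.
- The section 6.6 table marks the surveys at start and 10 months only, and the month-4 form has no survey page.
- Section 7.3 does not list EQ-5D among the secondary variables, and section 9.4 does not use it.

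This affects any QALY calculation. Let u0, u4 and u10 be the EQ-5D values at baseline, 4 and 10 months, and assume straight lines between measurements:
- Three points: QALY = (4/12)(u0 + u4)/2 + (6/12)(u4 + u10)/2. The weight on u4 is 4/24 + 6/24 = 10/24.
- Two points: QALY = (10/12)(u0 + u10)/2. The total weight is 10/12 = 20/24.

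With three points, half the weight (10/24 of 20/24) falls on the month-4 value. With two points, that value is replaced by interpolation between baseline and 10 months. A two-point QALY is feasible but coarse, so whether surveys are done at 4 months needs to be settled.

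**Comparator wording**
The aim in section 9.4 speaks of the "impact on health-related quality of life of the telerehabilitation intervention compared to in-hospital rehabilitation and the control group". The trial has two arms, and in section 6.2 conventional in-hospital rehabilitation is the control group. The extra comparator is a clerical leftover.

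**The case against.** The strongest reply concerns the system cost. Section 9.4 says that intervention costs are included; the sentences that follow describe schedules and are not worded as a closed list. Section 9.3 provides for resources that have no official rate. The objective of a monthly cost for the extended programme fits poorly with costing two weeks only, and a detailed resource list may sit in a later analysis plan. This stands as far as it goes. A reader might infer that the platform and 38 weeks of monitoring are costed at nothing; the documents do not support that. What remains is that section 9.4 itemises one part of the arm, is silent on the rest, and names only the catalogue as its price source.

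On staffing, an assistant may be present without supervising, so the two sections may not flatly conflict. They still give different inputs to a costing and need to be aligned. The rise from 16 to 24 counts heads; an assistant need not cost what a physiotherapist costs, so it should not be read as a 50% rise in cost.

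On the effect measure, cost per unit of the primary outcome is a legitimate design, and making QALYs the main measure would be a preference. This also stands. The defect is only that the stated aim and the stated measure differ.

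**Conclusion.** The point holds as a limited inconsistency in a secondary objective. The clearest part is the mismatch between the quality-of-life aim and the activity-only effect measure, with EQ-5D already collected at baseline and 10 months. The system, garment and review time for weeks 3 to 40 are unlisted but could be covered by the general clause and the section 9.3 fallback. Control staffing is 24 or 16 staff-sessions depending on the section followed. No monetary size can be given, because the protocol contains no prices.

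Three stronger readings are tempting and should not be drawn.

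- That a system cost above the saved hospital sessions would reverse the result. Section 9.4 also counts emergency visits, admissions, revascularisations, unscheduled contacts and, in the social analysis, lost productivity; and a dearer, more effective arm yields a ratio, not a reversal.
- That visits and sessions are counted twice. This would depend on a pricing method the protocol does not state, and both arms are listed in the same way.
- That the section as a whole is tilted towards telerehabilitation. The effect measure and the comparator wording have no evident cost direction, the effect of the staffing depends on which section is right, and the system cost is unlisted, not excluded.

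**What to change.** 1. In section 9.4, add an EQ-5D-based effect measure from baseline to 10 months, adjusted for baseline EQ-5D, alongside METs-minutes/week. Reconcile section 6.5 with the section 6.6 table and the month-4 form on whether surveys are done at 4 months, and state that a QALY rests on two time points if they are not.
2. Name the system licence, the patient device and professional review time in weeks 3 to 40 as telerehabilitation costs, and refer to the section 9.3 fallback for items without a catalogue rate.
3. Reconcile the control staffing in sections 6.4 and 9.4 with what is actually provided.
4. Delete the separate control group from the comparison in section 9.4.

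The cost is mostly wording. No new instrument is needed, but the platform price and a record of review time must be obtained, and any cost advantage reported for telerehabilitation may become smaller.
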